### III. Hypothesis or Study Goals (questions hoped to be answered by study):

The overall goal of the study is to evaluate the efficacy of a new smartphone-based technology for tracking and enhancing medication adherence. The technology, AGATE (Adaptive Goal-Directed Adherence Tracking and Enhancement), was recently developed by our colleagues at Talaria, Inc. (Seattle, WA) for the purpose of enhancing medication adherence for individuals with alcohol problems. In the current study we will test the efficacy of AGATE for increasing medication adherence in an eight-week pharmacotherapy study of naltrexone. Participants will be randomly assigned to smartphone-based adherence support (AGATE) or a control condition (smartphone alcohol and side effects diary, SASED). A secondary goal is to examine medication effects on patterns of daily drinking using ecological assessments permitted by cell-phone assessments.

The specific hypotheses are as follows:

**Hypothesis 1:** Those assigned to the AGATE condition will be more likely to be classified as adherent to naltrexone (e.g., taking 80% or more of scheduled doses) over the course of the study compared to those assigned to SASED.

**Hypothesis 2:** Those in the AGATE condition will take significantly more scheduled doses compared to those in SASED.

**Hypothesis 3:** Those in the AGATE condition will show better drinking outcomes (defined as higher percentage of days abstinent, lower percentage of heavy drinking days, fewer drinks per drinking day, and longer latency to first heavy drinking day) compared to SASED.

**Hypothesis 4:** Those in the AGATE condition will report higher satisfaction with treatment compared to SASED.

**Hypothesis 5:** Medication adherence will moderate the effect of naltrexone on drinking outcomes, such that the effects of naltrexone on reduced heavy drinking will be increased among those with higher rates of adherence.

**Hypothesis 6:** Adherence outcomes will mediate the effects of condition assignment (AGATE vs. SASED) on drinking outcomes.

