Alcohol use has been established as a significant factor in adherence to complex medication regimens (Galvan et al., 2002; Hendershot et al., 2009; Samet et al., 2007). Studies examining multiple levels of drinking (e.g., any vs. moderate vs. heavy use) have reported a linear relationship between drinking severity and nonadherence (Braithwaite et al., 2005, Samet et al., 2004; Tucker et al., 2003). Additionally, studies have linked temporal increases in patient drinking with greater non-adherence (Braithwaite et al., 2005; Spire et al., 2002). Finally, a recent meta-analysis confirmed the dose-response association of alcohol use with medication nonadherence in an analysis of 40 published studies totaling over 25,000 participants (Hendershot et al., 2009). With few exceptions (e.g., Parsons et al., 2007; Samet et al., 2004), medication adherence interventions have seldom focused specifically on individuals with alcohol use disorders (AUDs). Importantly, while three FDA-approved medications exist for treating alcohol use disorders (naltrexone, acamprosate, disulfiram), nonadherence is a specific barrier to the efficacy of these medications, partly due to the association of alcohol use with medication non-adherence. Given this barrier, further research is needed to a) investigate patterns and correlates of adherence to pharmacotherapy among those with alcohol use disorders, and b) to maximize medication adherence among heavy drinkers who are initiating pharmacotherapy.

Naltrexone is one of three FDA-approved medications for alcohol dependence. Naltrexone not only shows efficacy for reducing levels of alcohol use in alcohol-dependent individuals (Anton et al., 2006) but appears to reduce heavy drinking in non-dependent individuals with high-risk drinking patterns (Kranzler et al., 2003). However, naltrexone is only effective for some individuals and adherence to naltrexone has been identified as a key barrier to maximizing treatment efficacy. Because naltrexone is a front-line pharmacotherapy for alcohol dependence, the identification and remediation of barriers to naltrexone adherence could potentially lead to improved clinical outcomes in a substantial number of heavy-drinking individuals.

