Feinn et al. (2003) conducted a well-designed study to evaluate multiple methods of measuring medication adherence in the context of naltrexone treatment for problem drinking. One hundred fifty heavy drinkers ( $\geq 24$  standard drinks per week for men, and  $\geq 18$  standard drinks for women) were randomly assigned to receive naltrexone (50 mg once per day) or placebo for 8-weeks. Adherence was measured in all participants using electronic medication electronic monitoring system (MEMS; which records opening of a medication bottle); biweekly pill count, and self-reports using paper-and-pencil diaries. The highest rate of medication adherence was indicated by the diaries ( $M = .908$ ,  $SD = .146$ ), followed by MEMS ( $M = .873$ ,  $SD = .170$ ), and pill count ( $M = .857$ ,  $SD = .170$ ). The authors concluded that the daily diary method provided adherence data that was similar to that provided by the MEMS and that pill counts were less useful than either of the other approaches. AGATE is, in part, an electronic diary of adherence. Therefore, we have chosen to follow Feinn et al.'s design, with the exception of not including a placebo condition (our goal is not to evaluate efficacy of naltrexone versus placebo because this has already been demonstrated).

ii) Identify specific knowledge gaps which research is intended to fill (rationale for performing the research).

Our colleagues at Talaria, Inc. have developed a new medication adherence tracking system, AGATE (Adaptive Goal-directed Adherence Tracking and Enhancement). AGATE is designed to measure and maximize medication adherence and is delivered using smartphone technology. Talaria, Inc recently completed a Phase I Small Business Innovation Research (SBIR) trial (funded by the National Institute on Alcohol Abuse and Alcoholism, NIAAA) to develop AGATE as a method of tracking and enhancing medication adherence among individuals with alcohol problems. During that trial, [name] and colleagues developed a prototype of the AGATE system and conducted usability testing. Subsequently, NIAAA invited researchers at Talaria to submit a Phase II SBIR

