#### Overview of Naltrexone Trial

The purpose of the study is to evaluate whether AGATE effectively measures and enhances medication adherence in the context of a naltrexone trial involving heavy drinkers. Participants will be heavy drinkers recruited from the greater Albuquerque area who are interested in either reducing or stopping their drinking and deemed to be candidates for naltrexone pharmacotherapy by the study physician, [name]. Those enrolled in the study will be prescribed naltrexone (at FDA-approved dose of 50mg once daily) for eight weeks. All participants will receive smartphones during the study. Participants will be randomly assigned to receive either AGATE (adherence support) or SASED, a web-based alcohol and side-effects diary via smartphone. The primary outcome will be percent of scheduled doses that were taken during the eight week trial, as measured by the Medication Event Monitoring System (MEMS, Aardex Group, Union City, CA), pill counts, and the timeline follow-back (TLFB) method. The secondary outcomes will be selected indicators of alcohol use over the 8-week trial.

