Following completion of questionnaires the participant will meet with the study coordinator for detailed instruction on using the study cell phone and responding to prompts delivered by the cell phone. The participant's URSI number (which will have been randomly generated using the procedures outlined above) will be entered into the AGATE/SASED administrative interface, where computerized randomization will occur. This system is maintained by Talaria, but accessible via a web interface by the study research assistant using a secure password. At this time the participant will be asked to select a drinking goal: abstinence or moderation (moderation will be defined by the participant). Once the URSI number is entered, the computer randomization algorithm will block participants according to gender and drinking goal (abstinence or moderation), ensuring even distribution of these variables between conditions. The study coordinator will provide the participant with a study smartphone (Blackberry 8330 or equivalent) and instruct the participant in its use. This will include basic functions of the phone, how to respond to SMS prompts, and guidelines for acceptable use of the phone during the study (described below). Participants will also provide a saliva sample for analysis of a genetic variant in the mu opioid receptor gene (OPRM1 A118G, rs1799971), which is demonstrated to influence response to naltrexone (Anton et al., 2008; Ray & [name], 2007). Saliva will be collected in a plastic tube, labeled with the URSI number, and stored in a secure freezer in the neurogenetics lab at MRN. Samples will remain there until they are destroyed (10 years following study completion). Genetic analyses will be conducted in the neurogenetics lab at MRN. OPRM1 will be evaluated as a predictor of response to naltrexone in secondary analyses.

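### Hypothesis 5 asks whether adherence moderates the effect of naltrexone, but everyone is prescribed naltrexone; only a non-randomised association between doses taken and drinking can be estimated

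*Protocol*

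**What the plan says.** Section III of the protocol lists six hypotheses. The fifth is that "Medication adherence will moderate the effect of naltrexone on drinking outcomes", with a larger reduction in heavy drinking expected at higher adherence. The same section adds: "A secondary goal is to examine medication effects on patterns of daily drinking", using the phone assessments. The Procedures text in Section V, and again the biological-samples item of that section, plan a genetic analysis: "OPRM1 will be evaluated as a predictor of response to naltrexone in secondary analyses".

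On the design, the Overview of Naltrexone Trial says: "Those enrolled in the study will be prescribed naltrexone". The randomised factor is the phone program alone: "Participants will be randomly assigned to receive either AGATE (adherence support) or SASED". Section IV explains that the trial follows a cited eight-week study "with the exception of not including a placebo condition (our goal is not to evaluate efficacy of naltrexone versus placebo". No untreated, placebo or external comparison group is described anywhere.

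Two further items matter. Section IV says of earlier studies that they "have reported a linear relationship between drinking severity and nonadherence". Section V provides a time-stamped record of each opening of the pill container (MEMS) and a daily drinking report that is the same in both arms.

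**The concern.** A moderator changes the size of an effect. To show that adherence moderates the effect of naltrexone, one needs the difference in drinking between naltrexone and no naltrexone, and then evidence that this difference grows with adherence. The design removes the first of these. What remains is a slope of drinking on adherence within a group that is all prescribed the drug.

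That slope has more than one possible source. Doses taken may reduce drinking. Drinking may lead to missed doses. People with a better outlook may both drink less and take their tablets. Adherence is observed after randomisation and is not itself randomised, so the design does not separate these sources. At stake is what the trial may conclude: a negative slope would fit Hypothesis 5 as worded, yet would not show that the drug works better in adherent people.

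**Working it through.** **The plan's own figures.** The protocol gives no effect size, alpha or power for Hypothesis 5, so none is in dispute. Its recruitment figures (Section VI, item ii) reproduce: 140 × (1 − 0.25) = 105 randomised. With 88 at endpoint, attrition is 1 − 88/105 = 16.2%.

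**Step 1: is the moderation term estimable?** Let N be assignment to naltrexone (1 = yes), A adherence and Y drinking. Hypothesis 5 as worded corresponds to

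E[Y] = b0 + bN·N + bA·A + bNA·N·A,

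and claims that bNA differs from zero. With N = 1 for everyone this becomes

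E[Y] = (b0 + bN) + (bA + bNA)·A.

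The data give two numbers, an intercept and a slope, for four unknowns. The naltrexone effect merges with the intercept, and the moderation term merges with the adherence slope. A numerical check at n = 88 agrees: the four-column design matrix has rank 2 when N = 1 for all, and rank 4 with a hypothetical randomised placebo arm. A larger sample does not change this.

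**Step 2: what can be estimated?** The slope bA + bNA can. Here bA is whatever relation adherence has with drinking apart from the drug, and the protocol gives reason to think that it is not zero (the quoted relation between drinking severity and non-adherence).

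A contrast at dose level also exists. Suppose adherence equalled the MEMS mean of the cited eight-week study, 0.873 (an assumption for this trial). Then 88 participants × 56 days × (1 − 0.873) ≈ 626 person-days would pass without a recorded dose. Dosed and undosed days can therefore be compared, but the comparison is not randomised.

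**Step 3: how much could confounding matter?** The protocol gives no figure, so this is an illustration under assumptions. Let the true drug effect be zero, and let adherence and drinking correlate at ρ for other reasons. Test the correlation two-sided at 5% with n = 88 (20,000 simulated trials):

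| Assumed ρ | Trials with a significant result |
|---|---|
| 0 | 5% |
| −0.1 | 16% |
| −0.2 | 48% |
| −0.3 | 82% |
| −0.4 | 98% |

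The table shows how sensitive the test is to ρ. It does not say which ρ applies here.

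**Step 4: could the randomised phone program rescue the claim?** In principle AGATE could serve as an instrument for adherence. Take 44 per arm and SD 0.170 (the MEMS value from the cited study). The standard error of the difference in adherence is 0.170 × √(2/44) = 0.0362. The expected first-stage F is about (shift/0.0362)² + 1. For assumed shifts of 5, 8 and 10 percentage points this gives about 2.9, 5.9 and 8.6, which is weak. Such an analysis is not described in the protocol. It would also need AGATE to affect drinking only through doses taken, and it would estimate an effect of doses taken, not moderation.

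**The case against.** The strongest reply is that being prescribed a drug is not the same as taking it. MEMS time-stamps openings, drinking is reported daily, and missed doses create exposed and unexposed days. A reader might infer from Step 1 that this trial can say nothing about naltrexone and drinking at any sample size. The documents do not support that: the rank result concerns assignment to naltrexone, and a dose-level contrast does exist. This part of the reply stands. In that contrast, however, adherence is the exposure and not a moderator, and it is not randomised, so it supports a reworded hypothesis and not the present one.

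Second, Hypothesis 5 also predicts a direction: less heavy drinking with higher adherence. That can be tested as an association. Only its reading as a change in the drug's effect is unsupported.

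Third, the secondary goal is tied to day-level phone data, and the OPRM1 text speaks of a predictor, not of an interaction. Both can fairly be read as concerning drinking while on naltrexone. This stands, so they call for clarification only.

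Fourth, a reader might infer that the same slope would appear with an inert tablet. The documents do not show this. Section IV reports an association between drinking and non-adherence, including links over time. That makes reverse causation plausible but does not fix its size. The percentages in Step 3 rest on assumed correlations.

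Finally, modelling detail often belongs in a statistical analysis plan, which is not at hand. That is true of the lagging and adjustment suggested below. It does not cover the hypothesis itself, because no analysis plan can supply a comparison that the design lacks.

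**Conclusion.** The point holds for Hypothesis 5. As worded it concerns a naltrexone-by-adherence effect that cannot be estimated, because 0 of the 105 planned participants are assigned to anything other than naltrexone. This follows from the protocol's own text and needs no numerical assumption. What remains is an association between doses taken and drinking. Part of it may reflect drinking leading to missed doses; how large that part is cannot be derived from the documents.

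The secondary goal and the OPRM1 analysis share the limitation in a milder form. Drinking on naltrexone, and its relation to genotype, can be described, but drug response cannot be separated from prognosis.

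A reader might infer that the trial as a whole is compromised. It is not. Hypotheses 1 to 4 compare AGATE with SASED as randomised, and the primary outcome, the share of scheduled doses taken, does not depend on a drug effect. Hypothesis 6 is a separate mediation question and is not judged here. The correction matters because it changes what may be concluded from one of six stated hypotheses.

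**What to change.** 1. Reword Hypothesis 5, for example: *Among participants all prescribed naltrexone, higher MEMS adherence will be associated with less subsequent heavy drinking.*
2. Test it with dose-taking placed before the drinking period that it is meant to predict. Separate each person's mean adherence from the daily deviation around that mean, and adjust for prior drinking. This reduces the scope for reverse causation and for differences between persons, but does not remove them.
3. Report the result as an association and not as moderation of a drug effect.
4. Add a sentence to the secondary goal and to both statements of the OPRM1 analysis, saying that they concern drinking outcomes while on naltrexone and cannot separate drug response from prognosis.

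The change is mainly one of wording. MEMS time stamps and daily drinking reports are already to be collected, and no visit, treatment or sample size changes. The price is a weaker claim for Hypothesis 5 and slightly more analysis work.

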### IV. Background:

- i) Describe relationship of proposed study to previous investigations in the field, summarize those previous studies, including previous human, laboratory, and animal studies (describe existing knowledge).

Non-adherence to prescribed medications remains a significant and persistent barrier to the successful management of chronic medical conditions. It is estimated that non- or sub-optimal adherence accounts for 33-69% of medication-related hospital admissions at an annual cost of \$100 billion to the U.S. health care system (Osterberg & Blaschke, 2005). Non-adherence not only undermines treatment effectiveness on an individual basis but can also pose a threat to public health by promoting the development of drug-resistant pathogens (Paterson et al., 2000). The intransigent nature of non-adherence is illustrated by the modest adherence rates observed under even optimal conditions: clinical trials designed to maximize medication compliance among patients with chronic conditions have reported adherence rates ranging from 43 to 78% (Osterberg & Blaschke,

2005).

Alcohol use has been established as a significant factor in adherence to complex medication regimens (Galvan et al., 2002; Hendershot et al., 2009; Samet et al., 2007). Studies examining multiple levels of drinking (e.g., any vs. moderate vs. heavy use) have reported a linear relationship between drinking severity and nonadherence (Braithwaite et al., 2005, Samet et al., 2004; Tucker et al., 2003). Additionally, studies have linked temporal increases in patient drinking with greater non-adherence (Braithwaite et al., 2005; Spire et al., 2002). Finally, a recent meta-analysis confirmed the dose-response association of alcohol use with medication nonadherence in an analysis of 40 published studies totaling over 25,000 participants (Hendershot et al., 2009). With few exceptions (e.g., Parsons et al., 2007; Samet et al., 2004), medication adherence interventions have seldom focused specifically on individuals with alcohol use disorders (AUDs). Importantly, while three FDA-approved medications exist for treating alcohol use disorders (naltrexone, acamprosate, disulfiram), nonadherence is a specific barrier to the efficacy of these medications, partly due to the association of alcohol use with medication non-adherence. Given this barrier, further research is needed to a) investigate patterns and correlates of adherence to pharmacotherapy among those with alcohol use disorders, and b) to maximize medication adherence among heavy drinkers who are initiating pharmacotherapy.

Naltrexone is one of three FDA-approved medications for alcohol dependence. Naltrexone not only shows efficacy for reducing levels of alcohol use in alcohol-dependent individuals (Anton et al., 2006) but appears to reduce heavy drinking in non-dependent individuals with high-risk drinking patterns (Kranzler et al., 2003). However, naltrexone is only effective for some individuals and adherence to naltrexone has been identified as a key barrier to maximizing treatment efficacy. Because naltrexone is a front-line pharmacotherapy for alcohol dependence, the identification and remediation of barriers to naltrexone adherence could potentially lead to improved clinical outcomes in a substantial number of heavy-drinking individuals.

Feinn et al. (2003) conducted a well-designed study to evaluate multiple methods of measuring medication adherence in the context of naltrexone treatment for problem drinking. One hundred fifty heavy drinkers ( $\geq 24$  standard drinks per week for men, and  $\geq 18$  standard drinks for women) were randomly assigned to receive naltrexone (50 mg once per day) or placebo for 8-weeks. Adherence was measured in all participants using electronic medication electronic monitoring system (MEMS; which records opening of a medication bottle); biweekly pill count, and self-reports using paper-and-pencil diaries. The highest rate of medication adherence was indicated by the diaries ( $M = .908$ ,  $SD = .146$ ), followed by MEMS ( $M = .873$ ,  $SD = .170$ ), and pill count ( $M = .857$ ,  $SD = .170$ ). The authors concluded that the daily diary method provided adherence data that was similar to that provided by the MEMS and that pill counts were less useful than either of the other approaches. AGATE is, in part, an electronic diary of adherence. Therefore, we have chosen to follow Feinn et al.'s design, with the exception of not including a placebo condition (our goal is not to evaluate efficacy of naltrexone versus placebo because this has already been demonstrated).

ii) Identify specific knowledge gaps which research is intended to fill (rationale for performing the research).

Our colleagues at Talaria, Inc. have developed a new medication adherence tracking system, AGATE (Adaptive Goal-directed Adherence Tracking and Enhancement). AGATE is designed to measure and maximize medication adherence and is delivered using smartphone technology. Talaria, Inc recently completed a Phase I Small Business Innovation Research (SBIR) trial (funded by the National Institute on Alcohol Abuse and Alcoholism, NIAAA) to develop AGATE as a method of tracking and enhancing medication adherence among individuals with alcohol problems. During that trial, [name] and colleagues developed a prototype of the AGATE system and conducted usability testing. Subsequently, NIAAA invited researchers at Talaria to submit a Phase II SBIR

proposal, which was funded in October 2010. The Phase II SBIR study will be a joint effort between Talaria, the Mind Research Network and UNM. The goal of the Phase II SBIR trial is to examine the efficacy of AGATE in the context of a trial of naltrexone for alcohol problems. The goal of the trial is to evaluate the efficacy of AGATE in the context of a pharmacotherapy trial that approximates a real-world treatment setting.

